### The Interventions

The two interventions in the study contain self-guided, interactive behavior change treatment courses based on state-of-the-art best practices, and both have been examined extensively in the literature [8,38-46].

In the literature, the Overcoming Depression course was previously known as *The Depression Center*, and the Overcoming Anxiety course was known as *The Panic Center*. Both had separate URLs. In 2019, they were each placed onto a single platform, along with other Evolution Health courses and brief interventions.

The two interventions have undergone several iterations since their onset. For example, The Panic Center is the first intervention noted in Eysenbach’s [10] *The Law of Attrition* article. In that iteration, the course contained a tunnel design with 12 successive sessions. The course now has a gamified, free-form matrix design.

Table 2 outlines each course’s current theoretical constructs and evidence base, and Table 3 outlines the main course components.

**Table 2 table2:** Theoretical constructs and evidence base.

Theoretical construct	Overcoming Depression course	Overcoming Anxiety course
Brief intervention	✓	✓
Cognitive behavioral therapy	✓	✓
Gamification	✓	✓
Health belief model	✓	✓
Motivational interviewing	✓	✓
Social cognitive theory	✓	✓
Targeting and tailoring	✓	✓

**Table 3 table3:** Main course components.

Course component	Overcoming Depression course	Overcoming Anxiety course
Avatar upload	✓	✓
Course completion certificate	✓	✓
Course worksheets	✓	✓
Gamified cognitive behavioral therapy course	✓	✓
*Getting Started* video	✓	✓
Goals exercise	✓	✓
Moderated community	✓	✓
Private messaging	✓	✓
Statistics extranet (for corporate clients)	✓	✓
Tailored depression and anxiety test	✓	✓
Therapist extranet	✓	✓

### Ethical Considerations

All data collection policies and procedures adhere to international privacy guidelines [47-49]. At registration, all members tick a checkbox to confirm that they consent to having their data used for research purposes and approve of the platform’s privacy policy.

The platform does not collect personally identifiable information except a user’s email address, which is required for registration confirmation and the retrieval of lost passwords. Email addresses are encrypted in a separate database and are not included in data reports.

### Power and Sample Size

Our goal is to obtain 0.95 power to detect a significant difference in the proportion of users who complete at least 1 cognitive behavioral therapy session between the two treatment groups (arm 2 vs arm 3). Based on a preliminary analysis of an early subsample of users from November 1 to December 9, 2021 (arm 1: n=510; power=3.14%; arm 2: n=484; power=5.79%) and a conventional α level (.05) for statistical significance, we would require a sample of 4224 users, with 1414 users in each treatment group. Multimedia Appendix 1 shows our study’s CONSORT-EHEALTH (Consolidated Standards of Reporting Trials of Electronic and Mobile Health Applications and Online Telehealth) checklist [50].

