### Primary Outcome: Engagement With Tips and To-do Items

We will first measure engagement with the tips and to-do items in arms 2 and 3. We will compare the frequency of engagement with each nudge and behavioral prompt by age and gender. A member’s engagement with tips will be measured as the proportion of tips that were clicked. Specifically, it will be a value between 0 and 1, calculated as the number of tips that a member clicked divided by the number of tips that were presented to the member. Engagement with to-do items will be measured as the number of to-do items that a member clicked, and course component completion rates will be measured as the number of course components that a member completed. All comparisons between arms 2 and 3 will be conducted by using an independent sample 1-tailed *t* test; a conventional α level (.05) for statistical significance will be used.

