### Secondary Outcomes: Completion of Course Components

A secondary outcome of this experiment is to test whether the presentation of tips and to-do items increases the overall completion of course content. We will achieve this by comparing course component completion rates in arm 2 and arm 3 via a 1-way ANOVA in which the types of tips are used as the independent variable. We will then assess if age and gender predict which type of tip is the most engaging by using multiple regression.

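### The 0.95 power is calculated for completing at least 1 CBT session, which no planned analysis tests, and the primary outcome is several unranked measures, one of them listed again as secondary

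*Protocol article*

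**What the plan says.** Power and Sample Size (Protocol article) states: "Our goal is to obtain 0.95 power to detect a significant difference". The quantity is the "proportion of users who complete at least 1 cognitive behavioral therapy session", and the contrast is "between the two treatment groups (arm 2 vs arm 3"). The planning figures come from an early subsample, given as "arm 1: n=510; power=3.14%; arm 2: n=484; power=5.79"%. The result is "a conventional α level (.05) for statistical significance, we would require a sample of 4224 users, with 1414 users in each treatment group".

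The Primary Outcome section defines three measures:
- Tip engagement: "A member’s engagement with tips will be measured as the proportion of tips that were clicked".
- Number of to-do items clicked.
- Number of course components completed.

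It then says "All comparisons between arms 2 and 3 will be conducted by using an independent sample 1-tailed" t test at .05. It names no deciding measure and gives no multiplicity rule.

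The Secondary Outcomes section returns to completion, "comparing course component completion rates in arm 2 and arm 3 via a 1-way ANOVA". The Tertiary Outcomes section compares tip engagement by type of tip, also by ANOVA.

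Intervention Groups gives the to-do checklist to arm 3 only. In Table 4 (Data Collection), CBT session 1 is action code 2 of 14 tracked components.

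**The concern.** A power statement tells the reader how likely the trial is to detect a given effect in the analysis that decides it. Here it describes a binary comparison that the three outcome sections never make. A reader who sees 0.95 will credit the primary outcome with power that nobody has calculated for it.

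The primary outcome is also not a single quantity. Practical Implications makes the adoption of the arm 2 or arm 3 home page depend on whether members use the prompts, without saying which measure shows this. With several measures at .05 and no ranking, the chance of at least one false positive exceeds .05.

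Component completion appears under two ranks with two tests. A 1-tailed t test and a non-directional F test can fall on opposite sides of .05 with the same data, so the choice between them should not be left open.

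**Working it through.** **1. The plan's own figure.** The two percentages labelled as power are read as observed completion proportions: 16/510 = 3.14% and 28/484 = 5.79%. This reading is an assumption, but the counts fit it. Take p1 = 0.0314, p2 = 0.0579, mean 0.04465, difference 0.0265 and z = 1.645 for both one-sided .05 and 0.95 power:

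n = [1.645·√(2·0.04465·0.95535) + 1.645·√(0.0314·0.9686 + 0.0579·0.9421)]² / 0.0265² = 1313 per arm

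| Calculation at 0.95 power | n per arm |
|---|---|
| One-sided, no continuity correction | 1313 |
| One-sided, continuity correction | 1387 |
| Two-sided, no continuity correction | 1576 |
| Two-sided, continuity correction | 1651 |

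The one-sided corrected value is within 2% of 1414 (1387/1414 = 0.981). The other three are not close. At 1414 per arm and these rates, power is 96.2% one-sided and 92.7% two-sided. The size therefore fits a one-sided two-proportion comparison, and the arithmetic is not the fault. One caution is that the rates are labelled arm 1 and arm 2, while the powered contrast is arm 2 against arm 3. The power for that contrast rests on rates that the article does not attribute to it.

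**2. Where that endpoint is analysed.**

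| Section | Quantity | Test |
|---|---|---|
| Power and Sample Size | At least 1 CBT session (yes/no) | Two proportions (implied) |
| Primary | Tip-click ratio; to-do clicks; components completed | 1-tailed t test |
| Secondary | Component completion | 1-way ANOVA |
| Tertiary | Tip engagement by tip type | 1-way ANOVA |

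The first row has no counterpart below it. CBT session 1 is one of the 14 tracked components, but this gives the component count no stated power, because the article gives no mean, SD or target difference for that count.

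**3. What 1414 per arm gives a t test.** Detectable standardised difference = (z for α + z for power)·√(2/1414), with √(2/1414) = 0.0376:
- 1-tailed .05, as planned: (1.645 + 1.645)·0.0376 = 0.124 SD.
- Two-sided .05: (1.960 + 1.645)·0.0376 = 0.136 SD.

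These assume equal SDs and a usable value from all 1414 members in each arm.

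**4. Family-wise error.** Arm 2 has no to-do checklist, so two primary measures can be compared between arms. If independent, 1 − 0.95² = 0.0975, about 9.8%. By simulation of two correlated normal test statistics, each at one-sided .05, it is 9.3%, 8.8% and 7.5% at assumed correlations of 0.3, 0.5 and 0.8. The article gives no correlation. A positive one is plausible because the tips promote the components that are counted.

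**The case against.** Several points on the other side stand.

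- A reader might count three primary tests and infer a family-wise error of 1 − 0.95³ = 14.3%. The article does not support this, since to-do clicks have no comparator in arm 2.
- A reader might infer that no test keeps its stated error rate. Each t test alone is run at its stated .05, and the article never claims a family-wise .05. Only the overall error is uncontrolled.
- The CBT endpoint is not wholly absent, since session 1 is tracked and is one of the components that can be counted.
- The completion sentence in the primary section could be read as a definition for later use. On that reading only the tip-click ratio is compared between arms as primary, and the 9.8% falls away. However, the sentence assigning a t test to all arm 2 against arm 3 comparisons follows directly, so the text at best leaves rank and test ambiguous.
- Ranking and adjustment are often left to an analysis plan, which is not shown. That weakens the multiplicity point taken alone. It does not touch the mismatch between the endpoint that was sized and the outcomes that are listed, because the article states both.

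It is also tempting to make CBT completion the primary outcome because recruitment was sized on it. The documents speak against this. Strengths and Limitations gives engagement with prompts as the primary purpose, rates by arm had already been seen, and Results reports that data collection ended in May 2022. The switch would be a change of primary outcome informed by data.

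**Conclusion.** The concern holds in this form: the stated 0.95 power applies to none of the planned analyses, the primary measures are unranked, and component completion carries two ranks and two tests.

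The multiplicity part is modest. It is about 9.8% against a nominal 5% for two independent measures, and about 7.5% to 9.3% under the assumed correlations, provided that both measures are tested as primary. The early-subsample rates enter only the reproduction of 1414, not the mismatch itself.

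A reader might infer that the trial is underpowered for its primary outcome. The article does not show that. It gives no mean, SD or target difference for any primary measure, so the power of those tests is unknown. With 1414 per arm the design can detect 0.124 SD at 0.95 power in the planned 1-tailed test, and Results says that the required size was exceeded. The trial can be analysed as it stands. The plan does not say which result decides the question, or with what power.

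**What to change.** 1. In the Primary Outcome section, keep engagement with prompts as the purpose and name the tip-click ratio, arm 2 against arm 3, as the single primary outcome. Describe to-do clicks within arm 3 only.
2. List component completion once, as secondary, with one test.
3. In Power and Sample Size, keep the account of how 1414 was reached. Say that it was based on CBT completion and that the 0.95 power does not apply to the primary outcome. Add the detectable difference at 1414 per arm: 0.124 SD at 0.95 power for the 1-tailed t test (0.136 SD if the test is made two-sided).
4. Add the arm 2 against arm 3 two-proportion test of completing at least 1 CBT session as a named secondary analysis, with its sidedness stated. Disclose that CBT rates by arm were seen early.
5. Adjust the secondary tests by Holm.

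The cost is wording in three sections, with no new users or data. The power statement becomes less favourable, and the secondary measures face a stricter threshold. With two secondary tests, Holm's first step is .05/2 = .025. At that level and the planning rates, 1414 per arm gives the CBT comparison 92.7% power one-sided or 88.0% two-sided, subject to the arm-label caution above.

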### Randomization

During the registration process, by using a random number generator, new members will be assigned into 1 of the 3 arms (Figure 2). Randomization will be conducted by using simple randomization.

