### Intervention Groups

Members allocated to the first arm will be presented with a member home page that contains no behavioral prompts. Figure 3 is a screenshot of an arm 1 homepage for a member who chooses to engage with the depression course.

Members allocated to the second arm will be presented with a member page that contains a *Tip-of-the-Day* section containing directive content. The randomization strategy for the 35 directive tips is randomization without replacement. Figure 4 is a screenshot of an arm 2 homepage for a member who chooses to engage with the depression course.

Members allocated to the third arm will be presented with two sections that contain interactive prompts. The first is a *Tip-of-the-Day* section containing social proof and present bias content. At each log in, members will see a new tip. The randomization strategy for the tips is randomization without replacement. There are 15 social proof tips and 15 present bias tips.

In addition to the tips of the day, the third arm will also feature a to-do checklist that lists interactive course components. When a member clicks on an interactive component, they will be brought to the exercise. When they complete the exercise, the item is marked as complete with a check mark. Figure 5 is a screenshot of an arm 3 homepage for a member who chooses to engage with the depression course.

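### The 0.95 power stated for arm 2 vs arm 3 is not supported as printed: the planning rates are labelled arm 1 and arm 2, and no arm 3 rate is given

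*Protocol article*

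**What the plan says.** All of the sample size reasoning is in one paragraph of the protocol article, under Power and Sample Size.

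- Target, for completion of a CBT session: "Our goal is to obtain 0.95 power to detect a significant difference in the proportion of users who complete at least 1 cognitive behavioral therapy". The contrast is given as "between the two treatment groups (arm 2 vs arm 3").
- Planning data, from users registered between November 1 and December 9, 2021: "arm 1: n=510; power=3.14%; arm 2: n=484; power=5.79"%. The two percentages are called power but are evidently completion proportions: 16/510 = 3.14% and 28/484 = 5.79%.
- Result: "we would require a sample of 4224 users, with 1414 users in each treatment group". Alpha is .05, and this section does not say whether the test is one- or two-sided.

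Two other sections bear on how to read this. Intervention Groups defines the control: "Members allocated to the first arm will be presented with a member home page that contains no behavioral prompts". Arms 2 and 3 are the two prompt arms. The Primary Outcome section gives the sidedness of the arm 2 vs arm 3 comparisons: "All comparisons between arms 2 and 3 will be conducted by using an independent sample 1-tailed" t test.

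**The concern.** The target and the inputs name different pairs of arms. As labelled, the rates measure directive tips against no prompts, starting from about 3%. The power claim concerns one prompt page against another. If arm 2 is at 5.79%, that comparison starts from a higher rate, where the binomial variance is larger and the same absolute difference is harder to detect. The size of the arm 3 vs arm 2 difference is not stated at all.

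Arm 1 vs arm 2, the contrast that would carry the 0.95 as labelled, is not among the analyses in the three outcome sections, which all compare arms 2 and 3.

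Interpretation is at stake, not recruitment, because data collection has closed. Under Practical Implications, the arm 2 or the arm 3 page may become the default for all members. If arm 3 shows no advantage over arm 2 and the result is read against a stated power of 0.95, it would look like strong evidence that the pages perform alike. The printed inputs do not support that reading.

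**Working it through.** **Inputs.** From Power and Sample Size: rates 3.14% and 5.79%, alpha .05, target power 0.95, 1414 per group. Equal allocation is assumed from the equal group sizes. Both sidednesses are shown, because that section states neither and the Primary Outcome section specifies one-tailed tests.

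**Formulas** (two proportions, pooled variance under the null). Let d = |p₂ − p₁|, p̄ = (p₁ + p₂)/2, A = √[2p̄(1 − p̄)], B = √[p₁(1 − p₁) + p₂(1 − p₂)]. Then

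- n per arm = [(z_α·A + z_β·B)/d]²
- power = Φ[(d√n − z_α·A)/B]
- with continuity correction, n′ = (n/4)·[1 + √(1 + 4/(n·d))]²

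Here z_α = 1.645 one-sided or 1.960 two-sided, and z_β = 1.645 for 0.95 power.

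**Step 1: reproduce the plan's figure from 3.14% vs 5.79%.** d = 0.0265, p̄ = 0.04465, A = 0.2921, B = 0.2915.

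- One-sided: n = [(1.645 × 0.2921 + 1.645 × 0.2915)/0.0265]², which rounds up to 1313, or 1387 with continuity correction (within 2% of 1414).
- One-sided power at 1414: Φ[(0.0265 × 37.60 − 1.645 × 0.2921)/0.2915] = Φ(1.77) = 0.96. Fisher's exact test gives 0.957.
- Two-sided: n = 1576, or 1651 with correction. Power at 1414 is Φ(1.45) = 0.93.

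So 1414 is consistent with a one-sided calculation on these two rates. The difference labelled arm 1 vs arm 2 is what produced the sample size.

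**Step 2: the comparison named in the target.** Take the labels as printed, so arm 2 is 5.79%. The document gives no arm 3 rate, so each one below is an assumption, with arm 3 above arm 2 and 1414 per arm.

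| Assumed arm 3 rate | Power, one-sided | Power, two-sided |
|---|---|---|
| 6.79% | 0.29 | 0.19 |
| 7.79% | 0.68 | 0.56 |
| 8.44% (same 2.65-point step) | 0.86 | 0.78 |
| 9.0% | 0.947 | 0.904 |
| 9.5% | 0.98 | 0.96 |
| 10.68% (same ratio, 5.79/3.14) | >0.99 | >0.99 |

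Example, 8.44%: p̄ = 0.07115, A = 0.3636, B = 0.3631. One-sided power = Φ[(0.0265 × 37.60 − 1.645 × 0.3636)/0.3631] = Φ(1.10) = 0.86. At this rate, 0.95 power would take 2035 per arm one-sided or 2443 two-sided.

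**Step 3: detectable arm 3 rate at 1414 per arm, arm 2 at 5.79%.**

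| Power | One-sided | Two-sided |
|---|---|---|
| 0.95 | about 9.0% | about 9.4% |
| 0.80 | about 8.2% | about 8.5% |

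The 0.95 figures are relative rises over arm 2 of about 56% (9.03/5.79) and 62% (9.38/5.79).

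**Side check.** 3 × 1414 = 4242, whereas the stated total of 4224 is 3 × 1408. Using 1408 moves the powers above by less than 0.2 of a percentage point, so this discrepancy does not affect the point.

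**The case against.** The strongest reply is that the arm labels are simply wrong. The same parenthesis prints completion proportions as power, so its labelling is already unreliable. The preceding sentence speaks of two treatment groups, and numbering those 1 and 2 would produce exactly this text. On that reading the rates are from arms 2 and 3, and 1414 per group gives 0.96 one-sided power for the stated contrast. Nothing in the article rules this out, so the objection stands as a live alternative. It does not rescue the printed text, which would then need its labels corrected.

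A reader might also infer that the trial is underpowered for arm 2 vs arm 3. The document does not support that. No arm 3 rate is given, and if arm 3 rose over arm 2 in the same ratio as arm 2 over arm 1, power would exceed 0.99. The Results section says the required size was exceeded in each arm without giving numbers, so 1414 is a floor.

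Nor should two-sided figures be presented alone. The plan specifies one-tailed arm 2 vs arm 3 comparisons, and the sample size reproduces only one-sided.

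Finally, the proportion completing at least one CBT session is not listed as a separate test in the outcome sections. Those use t tests, ANOVA and regression on click proportions, counts and component completion. The figures here therefore describe the endpoint that the sample size paragraph names, not the power of those analyses.

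**Conclusion.** The point holds as an inconsistency within the sample size paragraph. The 0.95 power for arm 2 vs arm 3 has no support as printed, because its inputs are labelled as a different pair of arms and nothing is assumed about arm 3. True power for that contrast is undetermined; it has not been shown to be low.

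The size depends on which reading is right. If the labels slipped, no power is lost. If they are correct, 0.95 holds only when arm 3 reaches about 9.0% one-sided (9.4% two-sided), and repeating the 2.65-point step gives about 0.86 (0.78 two-sided).

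These figures assume arm 2 at 5.79%, 1414 per arm, equal allocation, arm 3 above arm 2, and a pooled two-proportion test at .05.

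**What to change.** Check the source of the two early rates, then rewrite the paragraph in one of two ways.

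1. If the rates came from arms 2 and 3, correct the arm labels and call the percentages completion proportions rather than power. The power claim can then stay.
2. If they came from arms 1 and 2, state that 1414 per arm gives about 0.96 power one-sided (0.93 two-sided) for 3.14% vs 5.79% in arm 1 vs arm 2. Replace the 0.95 claim for arm 2 vs arm 3 with the arm 3 rate detectable when arm 2 is 5.79%: about 9.0% at 0.95 power and 8.2% at 0.80 power one-sided (9.4% and 8.5% two-sided). Call the percentages completion proportions here too.

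In either case, state the sidedness, consistent with the one-tailed tests in the Primary Outcome section.

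The cost is one rewritten paragraph and, under the second option, a less favourable power statement for arm 2 vs arm 3. No additional users are needed.

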### Randomization

During the registration process, by using a random number generator, new members will be assigned into 1 of the 3 arms (Figure 2). Randomization will be conducted by using simple randomization.

**Figure 2 figure2:**
[figure not shown]
Study flow.

### Intervention Groups

Members allocated to the first arm will be presented with a member home page that contains no behavioral prompts. Figure 3 is a screenshot of an arm 1 homepage for a member who chooses to engage with the depression course.

Members allocated to the second arm will be presented with a member page that contains a *Tip-of-the-Day* section containing directive content. The randomization strategy for the 35 directive tips is randomization without replacement. Figure 4 is a screenshot of an arm 2 homepage for a member who chooses to engage with the depression course.

Members allocated to the third arm will be presented with two sections that contain interactive prompts. The first is a *Tip-of-the-Day* section containing social proof and present bias content. At each log in, members will see a new tip. The randomization strategy for the tips is randomization without replacement. There are 15 social proof tips and 15 present bias tips.

In addition to the tips of the day, the third arm will also feature a to-do checklist that lists interactive course components. When a member clicks on an interactive component, they will be brought to the exercise. When they complete the exercise, the item is marked as complete with a check mark. Figure 5 is a screenshot of an arm 3 homepage for a member who chooses to engage with the depression course.

